
### Caregiver secondary outcomes

Caregiver strain will be measured by the Modified Caregiver Strain Index, a 13-item scale, with scores ranging from 0 to 26, where higher scores indicate a higher level of caregiver strain.[79] Caregiver preparedness will be measured by the Preparedness for Caregiving Scale, a 8-item scale, with scores ranging from 0 to 32, where higher scores indicate the caregiver feels more prepared for the caregiving role.[80]

### Demographic and clinical factors

In addition to the above listed measures, we will also collect data on demographics and clinical factors. Demographics will include age, sex, race/ethnicity, education, pre-injury occupation, insurance status, and annual income. Clinical factors (via chart review) will include TBI severity, length of stay, and comorbidities.

### Data collection

For aim 1, a trained, bilingual (English- and Spanish-speaking) research coordinator will collect all longitudinal data from treatment and usual transitional care management arm patient/family dyads in-person or by phone at the following 4 timepoints: 1) 24–72 hours pre-hospital discharge (baseline); 2) 8-weeks post-hospital discharge (this is intervention midpoint for treatment arm dyads); 3) 16-weeks post-hospital discharge (this is intervention endpoint for treatment arm dyads); and 4) 24-weeks post-hospital discharge (follow-up/maintenance timepoint for treatment arm dyads). The 24-week follow-up/maintenance timepoint will be used to assess short-term benefits maintained after completion of the intervention. We will use all outcome data collected to assess efficacy (Aim 1) of our primary outcome, patient QOL (change in SF-36 total score[64]), for our intervention, as well as for analysis of secondary outcomes. Dyads in both the treatment and usual transitional care management arms will complete the same data collection measures at the same time points to allow for comparison in the longitudinal analyses (see **Fig 1** for SPIRIT schedule of enrollment, intervention, and assessments).

For recruitment rates, the research coordinator will record the number of patient/family dyads eligible, approached, and consented to participate. Based on our feasibility study, our anticipated recruitment is ≥50% of participants approached to participate. For enrollment rates, the research coordinator will record the number of patient/family dyads recruited and enrolled into the intervention. Based on our feasibility study, our anticipated enrollment is ≥90% of participants recruited. For data collection rates, the research coordinator will record for each follow-up data collection timepoint: 1) number of patient/family dyads called and reached; 2) number of call attempts per patient/family dyad; 3) number of patient/family dyads reached but unable to provide information; 4) length of phone call; 5) day of week and time of day patient/family dyads participated; and 6) completeness of data collected. The research coordinator will obtain baseline data by in-person or by phone from dyads 24–72 hours pre-hospital discharge. At 8-, 16-, and 24-weeks post-hospital discharge, the research coordinator will call patient/family dyads to obtain follow-up data. Based on our feasibility study, our anticipated data collection rate at baseline is 100% of patient/family dyads; our anticipated data collection rate for 8- and 16-weeks post-hospital discharge is 80% of dyads. Finally, our anticipated data collection rate at 24-weeks post-hospital discharge is 65% of dyads. We proposed more conservative estimates for recruitment, enrollment, and data collection than rates seen in our feasibility study.[31, 32] Our team will review recruitment and follow-up rates weekly and identify strategies to improve recruitment, enrollment, and data collection. For participant engagement rates, in accordance with the protocol, the interventionists will document each study activity delivered to each dyad and the length of time it took to complete each activity, useful for determining intervention intensity. Based on our feasibility study, our anticipated participant engagement rate is 75% of all intervention activities.

For aim 2, semi-structured interviews with BETTER dyads will be conducted by phone to assess participants’ perspectives on participation; interviews will be conducted by a trained, bilingual (English- and Spanish-speaking) research coordinator. We will select 45 treatment patient/family dyads (N = 90) who received BETTER to provide perspectives on barriers and facilitators to participating in BETTER. We will sample dyads stratified by three participation levels/interviewee groups: 15 dyads who complete ≤25% of intervention activities, 15 who complete 50–75%, and 15 who complete >75%. This sample size is guided by NIH Stage Model for Intervention Development guidelines of including 15–30 participants per interviewee group.[83] Interview questions will be on advantages of participating in BETTER, what participants valued or perceived to be most helpful, as well as concerns, challenges, and disadvantages of participating in BETTER. The interview guide will be available in English and Spanish and will be piloted before use. Each private interview will take approximately 10 minutes, and will be audio recorded and transcribed and translated verbatim by the research coordinator.

For aim 3, the average cost of delivering the intervention per dyad will be quantified by arm along with the average total costs of transitional care costs (post-discharge health service use) reported over 16-weeks post-discharge by arm, and will be tested for differences between arms. BETTER’s total transitional care costs (inclusive of post-discharge health service use) will be calculated as these costs are expected to increase given the intervention activities regarding care coordination and promoting appropriate referrals to meet needs. The cost analysis will be conducted regardless of effectiveness findings. If BETTER is effective at increasing QOL, a budget impact analysis will be conducted to inform the feasibility of scaling BETTER at a health system level. This approach will consider intervention costs and total health care costs with a priori sensitivity analyses as described below. It will also incorporate the average EuroQol scores by arm, as an additional measure of QOL. Whereas not powered for a full cost-effectiveness analysis, descriptively evaluating the EuroQol will allow comparison to other trials supporting adults with TBI.

Intervention-related costs will be assessed using a micro-costing approach and will be detailed by intervention components. Intervention-related costs include labor costs. Capital costs, which will be minimal beyond office space and are fixed costs that would not change with a larger implementation of BETTER, will be omitted. Labor costs will include: 1) time of investigators to train the interventionists, 2) research coordinator time spent recruiting/enrolling study participants, and 3) interventionist time spent being trained for and delivering intervention activities. Hourly wage and fringe benefit rates will be applied to the time spent per task to derive total labor costs, assessed using salaries and study data. Other intervention costs (e.g., software modification, patient recruitment) will be based on specific personnel’s annual salary plus benefits. Interventionist time spent conducting the intervention will be tracked by study interventionists. Time spent by research team members (i.e., research staff, interventionist) conducting research activities, but that would not necessarily be incurred if BETTER were implemented in clinical practice, will be tracked as well, so these costs can be excluded from intervention costs. Total intervention costs will be divided by the number of patients in each study arm to derive per-patient intervention cost, though individual patient costs may vary by intervention intensity.

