### Sample size determination

Findings from the pilot study were combined with literature on the clinically meaningful difference in SF-36 total scores for patients with TBI between groups (0.3 standard deviations) to perform the power analysis for this study.[32, 87] For this study, a total of N = 356 individuals will provide 80% power for the study design described above (α = 0.05, two-tailed) to detect a small effect size between study arms (Cohen’s d = 0.18). A sample size of N = 356 represents 178 patient/family dyads with 89 dyads randomly assigned to the treatment arm and 89 dyads randomly assigned to the usual transitional care management arm. Based on our preliminary studies, we anticipate that 10% of eligible participants will decline participation and that 10% of recruited/enrolled participants will be lost to follow-up.[32] As such, to account for attrition, our enrollment goal is N = 436 individuals (218 patient/family dyads; 109 dyads per arm). It worth noting that the power calculations were performed only for the primary outcome, patient QOL changes in SF-36 total scores from baseline to 16 weeks post-hospital discharge, to test our central hypothesis. We powered this study to detect a small effect size to ensure we can detect the minimal clinically important difference.^31^

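### The Aim 2 interview bands are not contiguous: BETTER dyads completing more than 25% but less than 50% of activities cannot be selected, and no reason is given

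*Protocol article*

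**What the plan says.** The Data collection section of the protocol article describes the Aim 2 sample. The total is fixed: "We will select 45 treatment patient/family dyads (N = 90) who received BETTER". The purpose is "to provide perspectives on barriers and facilitators to participating in BETTER". The selection rule is also fixed: "We will sample dyads stratified by three participation levels/interviewee groups", namely "15 dyads who complete ≤25% of intervention activities, 15 who complete 50–75%, and 15 who complete >75" per cent. The group size is justified by "guidelines of including 15–30 participants per interviewee group".

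The same section states that "our anticipated participant engagement rate is 75% of all intervention activities". No spread around that figure is given. The pool from which Aim 2 dyads are drawn is the BETTER arm; under Sample size determination the enrolment goal is "218 patient/family dyads; 109 dyads per arm".

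The abstract says only that 45 dyads randomized to BETTER will be interviewed. No other section gives different bands, explains the missing range, or offers another route to an interview.

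**The concern.** The lowest band stops at 25% and the next begins at 50%. Because the three quotas use every place, there is no residual place for a dyad in between. This is not a detail left to a fuller document: the article itself fixes the bands, the quotas and the total, and staff who follow the text would pass over these dyads.

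The aim is to learn what hinders and what helps participation, and stratifying by participation level is the means chosen to capture the range of experience. Dyads in the omitted range took up part of BETTER but completed less than half of it, so they bear directly on that question. As written, 30 of the 45 interviewed dyads will have completed at least half of the activities, and the only lower group will have completed a quarter or less. The Discussion part of the abstract says the findings will guide the design of a multi-site trial, so a gap here could carry forward.

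A related practical question is whether the lowest band can be filled, given an anticipated engagement rate of 75%, and what happens if it cannot.

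**Working it through.** **Inputs.** From Data collection: bands ≤25%, 50–75% and >75%, 15 dyads each; total 45 dyads (90 people); anticipated engagement 75%. From Sample size determination: 109 dyads in the BETTER arm.

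**1. Reproduce the planned total.** 3 × 15 = 45 dyads and 45 × 2 = 90 people. Both match the article, and 45 − 45 = 0 places remain for dyads outside the bands.

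**2. Coverage.** Assign each whole percentage from 0 to 100 to the bands. The values 26 to 49 (24 values) fall in no band. No value falls in two bands. Exactly 25% and exactly 50% are covered. The omitted range is therefore >25% to <50%.

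**3. How many dyads this might be.** The article does not give the spread of engagement, so this step is an illustration. Read 75% as the mean across dyads and take a beta distribution with mean m = 0.75 and standard deviation s. Then k = m(1 − m)/s² − 1, a = m·k and b = (1 − m)·k. For s = 0.25, k = 0.1875/0.0625 − 1 = 2, a = 1.5 and b = 0.5. With F the cumulative distribution function, the expected counts are 109 × F(0.25), 109 × [F(0.50) − F(0.25)], and so on.

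| SD | ≤25% | >25% to <50% (omitted) | 50–75% | >75% |
|---|---|---|---|---|
| 0.10 | 0.0 | 1.5 | 49.0 | 58.5 |
| 0.15 | 0.2 | 7.4 | 40.6 | 60.8 |
| 0.20 | 2.1 | 12.3 | 31.2 | 63.4 |
| 0.25 | 6.3 | 13.5 | 22.8 | 66.4 |
| 0.30 | 11.9 | 11.6 | 15.6 | 69.9 |
| 0.35 | 17.9 | 8.0 | 9.2 | 73.9 |

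The omitted range holds about 1 to 14 dyads.

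**4. The lowest quota.** It needs 15/109 = 13.8% of the arm at ≤25%. The expected count runs from about 0 to about 18: below 15 for SDs up to 0.30 and above 15 at 0.35. Treating the 109 dyads as independent, the chance of having at least 15 is about 0 for SDs up to 0.20, 0.2% at 0.25, 21% at 0.30 and 81% at 0.35. These figures assume that every such dyad can be reached and agrees to an interview.

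**5. Effect of closing the gap.** With a middle band of >25% to 75%, the bands cover 0 to 100% and the total stays at 3 × 15 = 45 dyads. Selection in proportion to numbers within that band would give the omitted range a share of 7.4/(7.4 + 40.6) = 15% at SD 0.15, about 2 of 15 places, and 13.5/(13.5 + 22.8) = 37% at SD 0.25, between 5 and 6 of 15. Adding a fourth band of 15 instead would raise the total to 4 × 15 = 60 dyads (120 people).

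**The case against.** The strongest reply is that sampling well-separated participation levels can be a legitimate purposive choice in qualitative work. All groups are asked about concerns and disadvantages, the group likely to face the strongest barriers (≤25%) is sampled, and activity delivery is logged for every dyad. This has weight, but the article does not state that rationale, and only the lower two bands are separated: the upper two meet at 75%. A slip in one cut-point is equally plausible. In either case the text needs a correction or a reason.

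Three stronger readings are tempting, and the article does not support them.

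- A reader might infer that partly engaged dyads are shut out altogether. They are not. Those completing 50–75% have 15 places, and those at ≤25% who did some activities share another 15. Only >25% to <50% is omitted.
- A reader might infer that the omitted dyads began BETTER and then dropped away, and are the most informative group on barriers. A completion percentage says nothing about timing, since such a dyad may have engaged sporadically throughout. Nothing in the article ranks the groups by how informative they are.
- A reader might infer that the lowest band will fall short. That depends on the assumed spread; at SD 0.35 the expected count exceeds 15. A shortfall would also not necessarily breach the stated rationale, which counts participants: 15 dyads are 30 people, and 8 dyads (16 people) would still meet the minimum of 15.

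It is also fair to say that widening the middle band does not by itself guarantee interviews with the omitted group, as step 5 of the working shows. The fix therefore has to ask for them explicitly.

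**Conclusion.** The gap stands on the face of the text and needs no modelling: under the stated bands and quotas, a dyad completing more than 25% but less than 50% of activities cannot be interviewed, and no reason is given in an aim about barriers to participation. Its size is uncertain, at about 1 to 14 of 109 BETTER dyads. That range rests on a beta distribution, on reading 75% as a mean across dyads, on SDs of 10 to 35 points, and on full enrolment of the arm. On the same assumptions the lowest band could hold anywhere from about 0 to 18 dyads, so its quota is a risk to plan for and not a demonstrated failure. The consequence is confined to the qualitative aim. The primary outcome, the power calculation and the Aim 1 analysis are unaffected.

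**What to change.** Make the bands contiguous and keep 15 dyads in each, for example ≤25%, >25% to 75%, and >75%. State that the middle band will purposively include dyads from >25% to <50%. Add that if fewer than 15 dyads fall at ≤25%, the remaining places go to those nearest above that cut-point. If the omission is intended, state the reason instead.

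The cost is a sentence or two in the Aim 2 text, with the same 45 interviews and the same justification of group size. The small downside is a broader and more mixed middle band.

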### Ethical considerations

Ethical approval has been obtained from the Duke University Health System Institutional Review Board (Pro00112309), including approval for electronic, written consent, with plans for protection of confidentiality discussed.

### Recruitment, screening, and enrollment

Recruitment for this study will occur 24–72 hours before acute hospital care discharge to home. A trained, bilingual (English and Spanish-speaking) research coordinator will review the electronic health record daily to determine if eligible patients have been admitted to the hospital. The research coordinator will contact eligible patients in-person during the hospital stay or via phone to determine interest in participating and to explain the informed consent, clearly discuss the study purpose and planned activities, answer all questions, and conduct further eligibility screening for patients. Next, each patient with TBI will be asked to identify which family member they would like to participate in the study with them. The research coordinator will then contact the family member identified by the patient. If the family member is also interested, the research coordinator will explain the informed consent, clearly discuss the study purpose and planned activities, and answer all questions. Finally, the research coordinator will obtain a signed, electronic informed consent from both the patient and family member and will email each a copy for their own records. The primary threat to attrition in this study is loss to follow-up.[84] To reduce and prevent attrition, participants will each receive up to $250 ($50/data collection timepoint x 4 quantitative data collection timepoints [treatment & usual transitional care management arms] + $50 for qualitative interview [treatment arm only]) during the study period.

### Randomization

After written consent is obtained, patient/family dyads will be randomly assigned to one of the two study arms, the: (1) intervention or (2) usual transitional care management arm. Dyads will be randomly assigned to one of the two study arms, with stratification based on TBI severity. Due to the nature of the intervention, the participants, interventionists, and the investigators responsible for overseeing the BETTER intervention cannot be blind to the allocation of participants to each group.

### Data analysis

For Aim 1, a descriptive analysis will be initially performed by examining distributional properties of demographic and clinical variables both for the overall sample size, as well as stratified by whether the individual received BETTER or usual transitional care management. Similarly, data will be stratified by (1) primary language spoken, (2) racial/ethnic group, and (3) sex to ensure randomization was successful. Differences in categorical explanatory variables will be tested using chi-square techniques (or the Fisher Exact test, when appropriate); while differences in continuous explanatory variables will be tested using independent-samples t-tests (or ANOVA, when appropriate).

The effects of the two arms (treatment vs. usual transitional care management) on the primary outcome in this RCT will be estimated and compared using repeated measures ANOVA to support the central hypothesis that adults with TBI receiving BETTER will have higher QOL 16-weeks after hospital discharge than those receiving usual transitional care management. Similarly, for our secondary aims, we will further examine if such differences exist in SF-36 total scores between these groups, over time by (1) primary language spoken, (2) racial/ethnic group, and (3) sex. The primary analytic endpoint for Aim 1 is at 16-weeks post-discharge to assess the longevity and efficacy of our observed effects, consistent with previous literature.

The longitudinal design of this study also allows us to examine if effects are observed as early as 8-weeks post-discharge; and whether effects hold (or are further increased) at 16- and 24-weeks post-discharge. Thus, linear mixed-effects models (LMMs) will be conducted. The two arms (BETTER vs. usual transitional care management), will be analyzed as fixed effects and time will be analyzed as a repeated measures effect to examine whether these outcomes significantly change over time. Other main effects (primary language spoken, race/ethnicity, sex) will be incorporated as covariates during secondary analyses. All main effects and all interactions will be investigated for significance from the mixed-effects models.

For all the analyses, intent-to-treat approach will be adopted as pre-planned for main effect comparisons between (1) BETTER vs. usual transitional care management, (2) primary language spoken, (3) racial/ethnic group, and (4) sex. Also, the bootstrap interval estimates will be generated for comparisons in all the linear models when model assumptions are untenable.

For Aim 2, interview transcripts will be coded using conventional content analysis, a data analysis technique suitable in an area where little is known.[85] The qualitative team is well-versed in qualitative methods and will consist of three bilingual members. The team will first read through all translated transcripts to get a holistic sense of the data and write memos describing initial impressions.[85] The team will then independently code transcripts and meet to discuss and compare codes and reach consensus on discrepancies. Codes will be entered into a codebook, with code names and definitions and quotation exemplars. The codebook will evolve as coding continues. Similar codes will be grouped into themes.[85] Findings will be reported using thick description and quotation exemplars as evidence of findings. Several strategies will be utilized to increase trustworthiness and rigor of findings, including developing an audit trail, engaging in peer debriefing, and including detailed methods and context of our sample and data collection and analytical procedures in publications and presentations describing findings.[86]

For Aim 3, within each study arm, unadjusted and covariate-adjusted differences in intervention costs and health care costs by primary language spoken, racial/ethnic group, and sex will be evaluated. The primary analysis will be the unadjusted costs relying on randomization. To understand factors associated with any cost differences, secondary analysis will evaluate the association of patient characteristics with patient-level costs using a generalized linear model (SAS PROC GLM) with family and link function to fit the distribution of the outcome. If BETTER is effective at increasing QOL, budget impact will be evaluated by comparing the expected costs of system-wide intervention implementation. Expected costs will be estimated by calculating per patient incremental costs of the intervention and then multiplying by the number of eligible patients. Sensitivity analyses will assess the impact of varying the length, reach (that is, number of patients served out of total eligible patients expected), and timing of BETTER on fee-for-service (FFS) revenue eligibility. Probabilistic sensitivity analyses will be conducted using Monte Carlo simulations in Excel’s Crystal Ball.

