## Methods

### Study design

This will be a single-site, two-arm, randomized controlled trial of BETTER, a culturally- and linguistically-tailored, patient- and family-centered, behavioral, TBI transitional care intervention for diverse English- and Spanish-speaking patients with TBI and their families, compared to usual transitional care management. In addition to baseline assessments at 24–72 hours pre-hospital discharge for both groups, follow-up assessments will occur at 8-weeks, 16-weeks, and 24-weeks post-discharge from acute hospital care to home. Dyads in both the treatment and usual transitional care management arms will complete the same data collection measures at the same time points to allow for comparison in the longitudinal analyses (see **Fig 1** for SPIRIT schedule of enrollment, intervention, and assessments). The study design of the BETTER RCT is illustrated in detail (see **Fig 2** for RCT design). The RCT is registered with clinicaltrials.gov (NCT05929833) and is funded by the National Institutes of Health (Grant # R01NR020818).

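### The primary 16-week test is fixed as repeated-measures ANOVA with visits and tested term unnamed, which fits poorly with intention to treat at the expected 65–80% follow-up

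*Protocol article*

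**What the plan says.** In the Protocol article, Data analysis, the arms' effects on the primary outcome "will be estimated and compared using repeated measures ANOVA to support the central hypothesis". The same section states: "The primary analytic endpoint for Aim 1 is at 16-weeks post-discharge". It then turns to whether effects appear by 8 weeks and persist to 24 weeks, and for that purpose says: "Thus, linear mixed-effects models (LMMs) will be conducted". The mixed model is not named as the primary test. The section also commits to intention to treat: "For all the analyses, intent-to-treat approach will be adopted as pre-planned for main effect comparisons".

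Under Study design, "follow-up assessments will occur at 8-weeks, 16-weeks, and 24-weeks post-discharge from acute hospital care to home", so with baseline there are four SF-36 visits. The Data collection section expects 80% of dyads at 8 and at 16 weeks, and says "our anticipated data collection rate at 24-weeks post-hospital discharge is 65% of dyads". Sample size determination says the power calculation concerns "patient QOL changes in SF-36 total scores from baseline to 16 weeks post-hospital discharge, to test our central hypothesis".

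**The concern.** Two things are left loose in the one test that decides the trial. First, classical repeated-measures ANOVA needs a full set of scores for each patient on the visits entered. At the follow-up the plan itself expects, it sets aside randomised patients who have usable data. Second, the name of the method does not fix the hypothesis. The group term, the group-by-time interaction over four visits, and the interaction over baseline and 16 weeks are three different tests, with different patients and different power. Leaving that open permits a choice after the data are seen. A model that avoids both problems is already in the plan, but only in a follow-on role.

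**Working it through.** **Does the power statement reveal which ANOVA is meant?** Inputs from Sample size determination: 178 patients, d = 0.18 (f = d/2 = 0.09), two-sided alpha 0.05, 80% power. For the interaction over m visits with correlation r, the noncentrality is N·f²·m/(1 − r), with m − 1 and (N − 2)(m − 1) degrees of freedom.
- m = 4, r = 0.475: 178 × 0.0081 × 4/0.525 = 10.99, power 80.0%.
- m = 2, r = 0.64: 178 × 0.0081 × 2/0.36 = 8.01, power 80.4%.

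No correlation is stated, so either version can be made to fit and the visits cannot be inferred. Whether the sample size is right is a separate question and is not relied on here.

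**Who is analysed.** Inputs: 218 patients enrolled; 80%, 80% and 65% follow-up.
- With a 16-week score: 218 × 0.80 = 174.
- Complete on four visits, at most (nested losses): 218 × 0.65 = 142. Independent losses: 218 × 0.80 × 0.80 × 0.65 = 91. Lower bound: 218 × (0.80 + 0.80 + 0.65 − 2) = 55.
- 16-week scores discarded by a four-visit analysis: at least 174 − 142 = 32.
- Dropped by a two-visit analysis: 218 − 174 = 44. Of these, none have an 8-week score if losses are nested, and about 218 × 0.80 × 0.20 = 35 if they are independent. With the 10% loss used in Sample size determination, 218 × 0.90 = 196 remain and 22 are dropped.

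**What is tested.** Assume effects of 0, 0.15, 0.30 and 0.30 SD at the four visits. The four-visit group term then targets (0 + 0.15 + 0.30 + 0.30)/4 = 0.19 SD, not 0.30. The four-visit interaction can be driven by another visit. In simulation with no 16-week effect and 0.4 SD at 24 weeks, it was significant in 68% of trials, against 5% for a 16-week comparison. With baseline and 16 weeks only, the interaction is the between-arm test of change to 16 weeks.

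**Precision of the 16-week effect** (SD units, r = 0.5 assumed, loss at random, 218 × 0.80/2 = 87.2 per arm at 16 weeks and 218 × 0.65/2 = 70.9 complete):
- Four-visit completers, change score: √(2 × 2(1 − 0.5)/70.9) = 0.168.
- Two-visit change score: √(2 × 2(1 − 0.5)/87.2) = 0.151.
- Baseline-adjusted: √(2 × (1 − 0.5²)/87.2) = 0.131.

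Simulations with 109 per arm and monotone loss gave somewhat larger values in the same order: about 0.18, 0.155 and 0.137 (the last for a mixed model with common baseline). The two-visit to adjusted ratio is √(2/(1 + r)): 1.24 at r = 0.3, 1.15 at 0.5 and 1.08 at 0.7. A mixed model that leaves baseline free in each arm had a simulated standard error of about 0.15 for the 16-week contrast, so the gain over the two-visit change score comes from handling baseline.

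**Power for the effect pattern above** (loss completely at random, simulated):

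| Test | r = 0.5 | r = 0.7 |
|---|---|---|
| Four-visit group term | 20–29% | 16–25% |
| Four-visit interaction | 25–38% | 40–62% |
| Two-visit change | about 50% | 71–73% |
| 16 weeks, baseline-adjusted | about 62% | 78–79% |

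Ranges run from independent to nested losses.

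**Bias.** Assume usual-care dropout depends on the last score (0.8 log-odds per SD), BETTER dropout does not, and the true effect is 0.30. Change estimates came out at about 0.26–0.35. When loss is concentrated early, the two-visit change reached 0.38; reversing the direction of dropout mirrors this to 0.60 − 0.38 = 0.22. The mixed model stayed near 0.30. With the same mechanism in both arms, completer analysis and mixed model were both unbiased.

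**The case against.** The strongest reply is that the article never says all four visits enter. It ties the primary comparison to 16 weeks, powers change from baseline to 16 weeks, and takes up the 8- and 24-week questions under the mixed model. On that reading the ANOVA uses two visits, 24-week losses are irrelevant and the right contrast is tested. This stands. A reader might infer that the primary test must drop anyone with any missed visit and cannot address week 16; the text supports that only for a four-visit specification, which it does not state.

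A reader might also infer that completer analysis would nearly erase a real effect. In the dropout scenario above, the raw 16-week difference among four-visit completers fell to about 0.05–0.09 for a true 0.30. That comparison ignores baseline, whereas the powered outcome is change. With the dropout direction reversed it gave 0.51. Nor does the document establish arm-dependent dropout: BETTER dyads have weekly contact, but both arms have the same measures, time points and payment per assessment. The figure is not a fair measure of the harm.

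Finally, missing-data handling may sit in an analysis plan that is not shown. That is so, and its absence is not the complaint. The article does state the primary method, and gives the model that uses partial data another role.

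**Conclusion.** The point holds in a limited form and is worth fixing. The named primary method does not fit the intention-to-treat commitment at the plan's own follow-up rates, and it does not identify one test. On the unfavourable reading, at most 142 of 218 patients are analysed and the test is not the 16-week contrast. On the favourable reading the contrast is right, but about 44 patients are excluded and the standard error is roughly 15% above what a baseline-adjusted model gives. Bias is a modest possibility under assumed dropout, not a demonstrated fault. The patient counts follow from the document's rates; the correlations, effect pattern and dropout mechanisms are assumptions.

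**What to change.** Name the planned linear mixed model as the single primary analysis. It should use all randomised patients with any SF-36 data, with visit as a category, arm-by-visit terms, an unstructured within-patient covariance, and baseline either constrained equal between arms or adjusted for. State that the primary test is the arm contrast at 16 weeks and that the 8- and 24-week contrasts are secondary. Delete the repeated-measures ANOVA, or keep it as a sensitivity analysis with its visits and tested term named. Replacing the ANOVA without handling baseline would forgo most of the precision gain over a two-visit change score. The cost is protocol and analysis-plan wording, with no new data or patients; the change should be made before outcome data are seen by arm.
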